### Design

2.1

A randomized controlled trial design will be applied to obtain data from in total 140 subjects: (1) hippotherapy intervention group (IG) (approx. N = 70) and (2) control group (CG) (approx. N = 70). Within a project duration of two years and six months (01.01. 2024–30.06. 2026), both groups, IG and CG, are to be assessed during two separate study cycles with IG (N = 35) and CG (N = 35) in each study cycle. Each study cycle will consist of a twelve-week intervention period (1x hippotherapy/week) with a pre/post measurement and a six-week follow-up measurement (see Fig. 1). Before therapy begins, the population will be randomly and evenly assigned to one of two groups: IG or CG.

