### Intervention

2.4

Hippotherapy will be carried out once a week for 30 min additionally to patients‘ usual physio- and/or pharmacotherapy (1-2x/week). The vibrations of the horse's back and the rhythm of the horse's stride are being utilized to achieve physiological reactions to improve individual balance performance, mobility, muscle strength and an upright sitting position. It will be carried out as a complementary movement-therapeutic approach for study-related purposes and not part of the treatment routine of patients with MS in standard outpatient rehabilitation. Therapies are standardized according to the principles of DKThR and carried out by trained physiotherapists plus state-approved hippotherapy (DKThR)® license [8]. The Intervention manual for hippotherapy (DKThR)® can be found in Appendix A1. The CG will undergo their treatment as usual without additional hippotherapy. Treatment as usual is defined as the continuation of physiotherapy (1-2x/week) and/or pharmacotherapy. The physiotherapeutic treatment aims to improve individual mobility, build up reduced muscle strength, stretch shortened muscles and loosen tense muscles, as well as alleviate pain through massages and/or heat/cold/electrotherapy. This is supplemented by gait and mobility training (everyday mobility) as well as weight-bearing training, improved coordination and balance and stabilization training. The CG will be offered 5 hippotherapy sessions (30-min units once a week) as an incentive after completing the study and to ensure compliance with regard to ethical aspects. Changing inclusion and exclusion parameters will lead to a drop out. A change in medication or participation in another measure (e.g. study, rehabilitation activity) is not permitted during the trial. Participation in less than 9 out of 12 hippotherapy sessions will lead to a drop out. Pregnancy in participants will also lead to a drop out.

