
The secondary study endpoints will be examined using descriptive statistical methods. Furthermore, to complement the primary analysis, an analogous ANCOVA will also be performed for secondary study endpoints. For the quality of life questionnaire (MSQoL-54), an MCID of 1.5 and 2.5 points will be applied [39]. Three procedures are applied to analyze the study results: (1) the *modified* intention-to-treat population (*m*ITT), which comprises all registered patients who completed the pre-measurement and serves as the primary analysis set for this investigation. It represents a solution for managing complications as noncompliance or missing outcomes and therefore reflects the practical clinical scenario [40]. (2) The *per protocol* population (PP): This data set contains all patients who completed the study without or with very minor violations of the regulations according to the study program and is considered a sensitivity analysis. It is considered a protocol violation if less than 9 units of hippotherapy were completed. Analyses for primary and secondary endpoints will be conducted for *m*ITT and PP populations, whereas evaluations based on the PP-population will serve as sensitivity analyses. (3) The third data set includes the safety population and considers AEs; it includes patients who completed at least one treatment, as opposed to the treatment they were randomized to receive. Safety data (AEs) are summarized and documented according to type, severity, intensity and correlation [41].

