### Ethical aspects and monitoring

2.9

The trial will be conducted by researchers of the German Sport University (Cologne, Germany) together with Kamillus Hospital (Asbach, Germany). Study monitoring will be realized by a scientific partner institution (Medical School Berlin Germany(MSB)). It will ensure study quality and compliance with good clinical practice standards (GCP). Furthermore, the study will be designed and conducted in accordance with the German General Data Protection Regulation (GDPR) by the European Union. Unforeseen or adverse events in the therapy process will be documented by the therapists using the German version of the Serious Adverse Event (SAE) Report Form and forwarded to the study team within 24 h [41]. Important protocol amendments will be forwarded to the monitor, ethical committees and if relevant, to the participants directly after decision. Data will be stored on protected servers of the German Sports University Cologne in Germany. Data will be evaluated in a pseudonymized form by assigning a study number to each study participant. A separate list in which the study numbers are assigned to the participant data (name and contact details), as well as the declarations of consent, are only accessible to the leading hippotherapists at the study sites, e.g. to contact the patients as part of the treatment or in the event of revocation during the intervention time. For data analysis, only datasets that are coded with the study number will be processed. The assignment lists will be destroyed after the data collection has been completed and the research data will be destroyed after the usual retention period of 10 years. The included participants have the right to information (including the right to a free copy of the data), as well as correction and restriction of data processing in accordance with the GDPR.

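### The safety set is defined by completing rather than starting a treatment, so a patient whose first hippotherapy session is ended by an adverse event, with none completed later, falls outside it

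*Protocol article*

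**What the plan says.** Section 2.8 (Statistical procedures) names three analysis sets. On the last it says "The third data set includes the safety population and considers AEs", and it gives the entry rule as "it includes patients who completed at least one treatment, as opposed to the treatment they were randomized to receive". The planned output is descriptive: "Safety data (AEs) are summarized and documented according to type, severity, intensity and correlation".

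The same section uses the verb for sessions when it sets the per-protocol limit: "It is considered a protocol violation if less than 9 units of hippotherapy were completed". Section 2.4 (Intervention) gives the session schedule: "Hippotherapy will be carried out once a week for 30 min". On how events are recorded, section 2.9 (Ethical aspects and monitoring) says "Unforeseen or adverse events in the therapy process will be documented by the therapists", with no condition that the session was finished.

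**The concern.** A safety set is meant to hold everyone exposed to the treatment, because exposure is what puts a patient at risk. Here the gate is completion, and an adverse event can itself prevent completion. Consider a patient who starts the first session, has an event, is stopped and does not return. That patient was exposed and the therapist recorded the event, yet the patient has completed no treatment and does not meet the entry rule.

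The final clause of the rule contrasts treatment taken with treatment assigned. It settles which treatment a patient is counted under. It does not bring back a patient who completed none.

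The Discussion presents the collection of adverse events as a way to make the course and benefit of therapy more transparent. Eligible patients have an EDSS of 4 to 6, spasticity of the lower limbs and impaired balance, so an interrupted first session is plausible. An event that ends first exposure is among the more informative ones, and it is the one the literal rule leaves out.

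**Working it through.** The protocol states no adverse-event rate, so there is no figure to reproduce. The check has three parts.

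**1. The texts side by side**

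- Entry to the safety set (2.8): at least one treatment completed.
- The same verb in the per-protocol rule (2.8): it counts hippotherapy units. The natural reading of the entry rule is therefore at least one completed session. If treatment meant the whole 12-week course, the exclusion would be wider.
- Event recording (2.9): events during therapy are documented whether or not the session was finished.
- No section readmits a patient who started but did not complete a first session.

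The event therefore reaches the trial's records, while its patient does not reach the set that is summarised.

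**2. Direction**

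Let N be the patients exposed to hippotherapy, x those with at least one adverse event, and k those among the x whose event ended the first session and who completed no later one.

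- All exposed: x/N
- Completers of at least one session: (x−k)/(N−k)
- Difference: x/N − (x−k)/(N−k) = k(N−x) / [N(N−k)]

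The difference is positive whenever k ≥ 1 and x < N.

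A patient who stops the first session without an event also leaves the set, but this moves the proportion slightly upwards: 7/70 = 10.0% becomes 7/69 = 10.1%. The understatement comes only from stops caused by an event.

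**3. Illustration**

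N = 70 is the approximate size of the hippotherapy group in section 2.1 (Design). The values of x and k are assumptions.

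| x | All exposed | k = 1 | k = 2 | k = 3 |
|---|---|---|---|---|
| 1 | 1/70 = 1.4% | 0/69 = 0% | – | – |
| 3 | 3/70 = 4.3% | 2/69 = 2.9% | 1/68 = 1.5% | 0/67 = 0% |
| 7 | 7/70 = 10.0% | 6/69 = 8.7% | 5/68 = 7.4% | 4/67 = 6.0% |
| 14 | 14/70 = 20.0% | 13/69 = 18.8% | 12/68 = 17.6% | 11/67 = 16.4% |

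Check of the formula for x = 7, k = 1: 1 × 63 / (70 × 69) = 1.3 percentage points, which matches 10.0 − 8.7.

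The chance that at least one such patient occurs among 70 is 1 − (1−p)^70, where p is the assumed probability per patient: 30% for p = 0.5%, 51% for 1%, 76% for 2% and 88% for 3%.

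**The case against.** The strongest reply is that one loosely chosen verb is being read too strictly. Section 2.4 states the same nine-session limit in terms of participation, where section 2.8 speaks of completion, so the authors may use the two words interchangeably. The 30 minutes in section 2.4 is a schedule, and nothing defines a completed session as one that ran its full length. The as-treated clause also suggests that the authors had the conventional safety set in mind. This has weight: the intent may well be treatment received. But the document does not say so, and the rule as printed makes completion the condition. If received was meant, the correction only writes down the intent.

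A second reply is that this is a condensed article and a fuller document may define the set more precisely. That would answer a complaint about missing detail. The point here is a rule that the article does state.

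Third, the harm does not vanish. Events go to the study team within 24 hours, and section 2.6 sends medically relevant withdrawals to the monitor and the ethics committee. That is correct. What is at stake is the summary of adverse events, not their capture.

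Two stronger readings are tempting and are not supported:

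- A reader might infer that every patient hurt or stopped in the first session is lost. Patients who are hurt but finish, or who complete a later session, stay in the set, and stops without an event do not lower the proportion.
- A reader might infer that the adverse-event rate is understated as a matter of course. That requires at least one patient of the kind described and a literal application of the rule. The plan sets out a descriptive summary with no stated rate, bound or comparison between groups, so no planned figure can be called wrong.

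**Conclusion.** The point holds in conditional form. As written, the rule lets an adverse event decide whether its own patient is counted, in the narrow case of a first session ended by the event and no session completed afterwards. If any such patient occurs, the proportion of hippotherapy patients with an event is too low.

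The size cannot be derived from the documents. Over the assumed range above, the loss is about 1 to 4 percentage points with 70 exposed patients. This rests on three assumptions: completed is applied literally, treatment means a single session, and about 70 patients start hippotherapy. The change is worth making because the rule has no evident advantage and is easy to correct.

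**What to change.** Reword the definition in section 2.8. On the hippotherapy side, the safety set should hold all patients who started at least one hippotherapy session, completed or not, during the study period from baseline to follow-up, analysed by the treatment they actually received. The time window is needed because section 2.4 offers control patients five sessions after they complete the study, and those sessions should not move them into the hippotherapy set. The definition should also state that control patients enter under treatment as usual, since they have no study session by which to qualify.

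The cost is one sentence of text. Events are already recorded whether or not the session is completed, so no new data are needed. The only downside is that the summary of adverse events for hippotherapy may look slightly less favourable.

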### Ethical aspects and monitoring

2.9

The trial will be conducted by researchers of the German Sport University (Cologne, Germany) together with Kamillus Hospital (Asbach, Germany). Study monitoring will be realized by a scientific partner institution (Medical School Berlin Germany(MSB)). It will ensure study quality and compliance with good clinical practice standards (GCP). Furthermore, the study will be designed and conducted in accordance with the German General Data Protection Regulation (GDPR) by the European Union. Unforeseen or adverse events in the therapy process will be documented by the therapists using the German version of the Serious Adverse Event (SAE) Report Form and forwarded to the study team within 24 h [41]. Important protocol amendments will be forwarded to the monitor, ethical committees and if relevant, to the participants directly after decision. Data will be stored on protected servers of the German Sports University Cologne in Germany. Data will be evaluated in a pseudonymized form by assigning a study number to each study participant. A separate list in which the study numbers are assigned to the participant data (name and contact details), as well as the declarations of consent, are only accessible to the leading hippotherapists at the study sites, e.g. to contact the patients as part of the treatment or in the event of revocation during the intervention time. For data analysis, only datasets that are coded with the study number will be processed. The assignment lists will be destroyed after the data collection has been completed and the research data will be destroyed after the usual retention period of 10 years. The included participants have the right to information (including the right to a free copy of the data), as well as correction and restriction of data processing in accordance with the GDPR.

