### Outcomes

2.5

The primary endpoint of the study is the change in balance performance after 12 units of hippotherapy (change from baseline). To assess the primary outcome measure, the Berg Balance Scale (BBS) will be used in an independent assessment by a blinded observer (Table 5). Blinded assessors will be trained for collecting the BBS data prior to the start of the intervention by the investigators. Unblinding is not permitted during the trial. Assessors will be trained to collect EEG, force plate and Posturomed® data. Therapists at study centers will be educated and instructed on how to complete Adverse Event Report forms (AEs) and EQUITEDO® assessments.

**Table 5 tbl5:** Protocol Berg Balance Scale.

(0–4 points/sum score)
1. from sitting to standing
2. standing without support
3. sitting without support
4. from standing to sitting
5. transfers
6. standing with eyes closed
7. standing with feet close together (close foot stance)
8. reaching/longing forward with outstretched arm
9. picking up an object from the floor
10. turn around to look backwards
11. turn 360°
12. alternately place your feet on a footrest
13. standing with one foot in front of the other (tandem stand)
14. standing on one leg (one-legged stand)

As the gold standard for measuring balance in a clinical setting, the BBS enables the results of this therapy to be compared with other interventions, and is therefore applied as primary outcome measure [18,19]. In regard to validity and reliability, the BBS shows satisfactory values [[18], [19]].

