The secondary endpoints of the study will be the measurement of fatigue using the Fatigue Severity Scale (FSS) [27]. The FSS represents the gold standard for measuring fatigue [28]. In addition, the Multiple Sclerosis Quality of Life-54 Questionnaire is used as a disease-specific instrument (MSQoL-54), which supplements the SF-36 questionnaire for recording health-related quality of life with 18 MS-specific items [29]. The MSQoL-54 is a validated and established instrument in measuring quality of life in MS [29]. Pain will be measured using the visual analog scale (VAS) [30]. VAS is used because it represents a simple and frequently used method for measuring pain in clinical practice and is also regarded as a measure of the effectiveness of treatment and thus offers comparability to other studies [30]. Change in spasticity will be measured via Numeric Rating Scale (NRS) [31]. NRS is a validated and established instrument for the measurement of spasticity [31]. The self-assessment version of the ICF-based WHO Disability Assessment Schedule 2.0 (WHODAS 2.0) will be used to measure activity- and participation-related parameters [32]. WHODAS 2.0 is validated and links back to ICF domains [32]. In addition, an ICF-based EQUITEDO® assessment to be completed by the therapists as an external assessment will be used to document the process and results of the hippotherapy measures [33]. EQUITEDO® assessment is also validated and also linkable to ICF domains [33]. Furthermore, a self-constructed questionnaire for monitoring regularity, frequency, and content of the treatment as usual of both IG and CG across the full duration of the intervention (including follow-up) will be applied. Questionnaires will be filled out and processed digitally using two software programs Questback Unipark (Tivian XI Ltd., Cologne, Germany) and EQUITEDO® application (Research Institute for Inclusion through Physical Activity and Sports Ltd., Frechen, Germany).

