### Assessment

2.7

At baseline, post and follow-up, balance performance, BBS, EEG, quality of life, fatigue, pain, spasticity and activity- and participation-related parameters will be collected. The following table (Table 7) shows the time schedule of patient enrolment and intervention.

**Table 7 tbl7:** Time schedule.

	Registration	Baseline assessment	Post assessment	Follow-up assessment
Fulfillment of the inclusion criteria	X	12 weeks hippotherapy or 12 weeks treatment as usual		6 weeks treatment as usual
Written declaration of informed consent	X			
Medical clearance	X			
Assignment to the study group	X			
Anthropometric data	X			
Balance assessment/EEG		X	X	X
BBS		X	X	X
Quality of life (MSQoL-54)		X	X	X
Fatigue (FSS)		X	X	X
Pain (VAS)		X	X	X
Spasticity (NRS)		X	X	X
WHODAS 2.0 36-Self		X	X	X
EQUITEDO® (IG only)		X	X	

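### The only adverse event route described runs through the hippotherapists, so ascertainment differs by arm, stops before follow-up, and leaves the controls' place in the safety set unclear

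*Protocol article*

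**What the plan says.** Section 2.9 (Ethical aspects and monitoring) fixes who records events and where: "Unforeseen or adverse events in the therapy process will be documented by the therapists". It also names the form (the German SAE report form) and a 24-hour limit for forwarding to the study team. Section 2.5 (Outcomes) assigns the training to match: "Therapists at study centers will be educated and instructed on how to complete Adverse Event Report forms (AEs) and EQUITEDO® assessments". In the same paragraph, assessors are trained for the Berg Balance Scale, EEG, force plate and Posturomed, and no AE task is mentioned for them.

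The control arm is described in 2.4 (Intervention): "The CG will undergo their treatment as usual without additional hippotherapy". The timetable is in 2.1 (Design): "Each study cycle will consist of a twelve-week intervention period (1x hippotherapy/week) with a pre/post measurement and a six-week follow-up measurement". Table 7 in 2.7 (Assessment) labels the last stretch "6 weeks treatment as usual". That table has no AE row.

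The safety population is defined in 2.8 (Statistical procedures): "it includes patients who completed at least one treatment, as opposed to the treatment they were randomized to receive". AEs are then to be summarised by type, severity, intensity and correlation.

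One instrument does reach both arms throughout, follow-up included. Section 2.5 describes it as "a self-constructed questionnaire for monitoring regularity, frequency, and content of the treatment as usual of both IG and CG".

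**The concern.** The named recorder is present only where hippotherapy is delivered. A fall or relapse in a control patient, or in a hippotherapy patient after week 12, has no described path into the AE data. The same event in a hippotherapy patient during the 12 weeks may be seen by the therapist or mentioned at the next session. The chance that an event is recorded then depends on the arm as well as on whether it happened.

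The population makes this matter. Participants have MS with lower-limb spasticity, an EDSS score of 4 to 6 and impaired balance, so some events are to be expected whatever the treatment. Without a background rate collected in the same way, a count of events under hippotherapy cannot be divided into those due to therapy and those due to disease. The Discussion expects AE collection to add transparency about the course of therapy and its actual benefits. Data collected by this route can support that only weakly.

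**Working it through.** The plan gives no figure on this point, so there is none to reproduce. The check has two parts: how much observation time the described route covers, and whether anything else in the article fills the gap.

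**Inputs**
- About 70 patients per arm (2.1).
- 12 intervention weeks plus 6 follow-up weeks, 18 in all (2.1, Table 7).
- One 30-minute session per week (2.4).
- Assumption: no dropout.

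**Coverage**
- Planned observation: 140 × 18 = 2520 person-weeks.
- Upper limit of the described route (hippotherapy arm, whole intervention period, counting events reported to the therapist between sessions): 70 × 12 = 840 person-weeks; 840 / 2520 = 33.3%.
- No described route, control arm: 70 × 18 = 1260 person-weeks.
- No described route, hippotherapy arm in follow-up: 70 × 6 = 420 person-weeks.
- Total without a described route: 1260 + 420 = 1680; 1680 / 2520 = 66.7%.

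The 33.3% is a ceiling. If the setting is read strictly as the session itself, each patient contributes 12 × 0.5 h = 6 h. The arm then contributes 70 × 6 = 420 h, which is 420 / 168 = 2.5 person-weeks, or about 0.1% of 2520.

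**Other contacts in the article**
- The usual-treatment questionnaire (2.5) reaches both arms through follow-up, but its stated content is the treatment received, not events.
- The post and follow-up visits (2.7) see both arms, but no AE question is assigned to them.
- Medically relevant withdrawals go to the monitor and ethics committee (2.6). An event in a patient who stays in the trial is not covered.
- Pain, spasticity and fatigue scales are taken in both arms at all three time points. They show the state reported at those assessments. They do not count falls, injuries or relapses in between.

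**Safety set**
The definition in 2.8 contrasts treatment received with treatment assigned. That contrast is useful only if a patient can fall into more than one treatment category, which suggests two arms. Entry, however, requires one completed treatment, and the article does not say what that means for someone continuing usual care. Two readings remain. If controls are in, their events come from no described source. If controls are out, the set has one arm and no comparator.

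**The case against.** The strongest reply is that this is a condensed article. AE elicitation, time windows and the details of the safety set are commonly left to the full protocol or the analysis plan, and neither is shown. Nothing in the text says that therapists are the sole source. Both arms have study visits and questionnaires, withdrawals are reported, and the trial is monitored for GCP. No safety hypothesis is listed and no between-arm test is stated. A one-armed record of therapy-related events would be a limited but legitimate choice.

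Much of this stands. A reader might infer that no control-arm event can be captured at all. The documents do not support that: they describe one route and do not exclude others, and patients in both arms are seen at post and follow-up. A reader might also infer that the trial's safety comparison is invalid. The documents do not support that either, because 2.8 plans only a descriptive summary.

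The appeal to condensation does not dispose of the point, however. The article is not silent on AEs. It names the recorder, setting, form, deadline and training, and each of these is tied to the therapists or to the delivery of therapy. The safety set wording is ambiguous as it stands.

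**Conclusion.** The point holds in a limited form. AE ascertainment as described differs by arm and does not extend to the six follow-up weeks. It covers at most 840 of 2520 person-weeks (33%), assuming 70 per arm, no dropout, and therapists learning of every event in the 12 weeks. Whether controls belong to the safety set is not stated.

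The consequence concerns interpretation. A descriptive summary by arm would show more events under hippotherapy partly because someone was there to record them. A summary for hippotherapy alone would have no background rate. The size of any distortion cannot be given, because the article states no event rate. The primary balance analysis is not affected. If the full protocol already provides for AE elicitation in both arms through follow-up, what remains is to say so and to clarify the safety set.

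**What to change.** 1. Add one short AE block, identical in both arms (for example falls, relapses, injuries and hospital visits), to the usual-treatment questionnaire already given to both arms through follow-up. Ask it again at the post and follow-up assessments. Using the questionnaire rather than the blinded Berg Balance Scale assessor avoids patients revealing their allocation while describing an event. Add an AE row to Table 7.
2. Define the safety set to include controls, with patients classified by treatment received during the trial: at least one hippotherapy session versus none.
3. Report events that therapists observe in sessions in a separate table for the hippotherapy arm, and make no between-arm statement from that table.

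The cost is a few more items in an existing digital questionnaire and some rewording, with no extra staff or visits. The drawback is reliance on self-report and recall. The procedure is the same in both arms, so the counts are at least collected alike. The change is best made before further patients complete the study, because events not asked about at the time are hard to recover later.
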